### This Study

This study will examine a comprehensive multicomponent positive psychology-based self-help book with email support. The self-help book is entitled, “This is your life” (TL) [40] and targets 6 key components in positive psychology: positive emotion, use of strengths, optimism, self-compassion, resilience, and positive relations. We will compare a condition wherein participants receive the book with weekly asynchronous and tailored email support (TL-E) to a condition wherein participants receive the book with a weekly email with information (TL-I). Both groups will be compared to a waiting list control condition (WL). Our research aim is to evaluate the efficacy of the multicomponent self-help book with or without email support in terms of well-being and flourishing in an RCT (NTR4297) and to evaluate which of the included well-being components in the self-help book contribute to its efficacy. We expect that TL-E will be equivalent or superior to TL-I and superior to WL at post-test and 6 months follow-up, and that the effects will be sustained at 12 months follow-up.

This study will add to current knowledge in 3 ways. First, it will be conducted in a sample with low or moderate levels of well-being without moderate or severe clinical symptomatology, which is a potential “happiness-seekers” group [41] that has not previously been studied in PPIs [17,18,27]. Second, this study will gain insight into the working mechanisms underlying the intervention by evaluating which of the included well-being components in the self-help book (ie, positive emotion, use of strengths, optimism, self-compassion, resilience, and positive relations) contribute to its efficacy and by examining individual differences in demographic characteristics, number of life events, personality traits, and adherence rates. Third, this study will examine if the innovative format used in this study (ie, self-help book with relatively inexpensive email support) is a cost-effective approach for enhancing well-being and flourishing compared to a waiting list control group, since little is known about the cost-effectiveness of PPIs [26].

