### Statistical Analyses

The Consolidated Standards of Reporting Trials (CONSORT) statement [91] will be used to report the results. Independent *t* tests and Chi-square statistics (X^2^) will be used to examine baseline differences between the study groups. Non-significant socio-demographic differences at baseline will indicate successful randomization. Internal consistency of the constructs will be determined using Cronbach’s alpha. To examine the efficacy of the intervention, intention-to-treat analyses will be conducted by including all participants in the analyses who have been randomized. The Expectation Maximization (EM) method will be used to impute all missing data on the continuous measures of T1, T2 and T3. This method imputes the data by maximum likelihood estimation using the observed data in an iterative process [92]. The intention-to-treat analysis will be compared with a completers-only analysis.

To examine significant differences between the 3 groups, we will perform repeated measures ANOVA in a 3 (group) x 3 (time) design with well-being (MHC-SF and FS) as the primary dependent variable and positive/negative emotions (mDES), the use of strengths (SUS), optimism (LOT-R), self-compassion (SCS-SF), resilience (BRS), and positive relations with others (SPR) as the secondary dependent variables. Significant time x group interactions will be tested with Tukey’ post hoc tests. Within-group effects (Cohen’s *d*) will be calculated by subtracting the mean post-test or follow-up score from the mean baseline score and dividing the difference by the pooled standard deviation. Between-group effects (Cohen’s *d*) will be calculated by subtracting the mean post-test or follow-up score of the experimental group from the mean post-test or follow-up score of the control group, and dividing the difference by the pooled standard deviation [93]. These effect sizes are used to gain insight into the relevance of the significant effects. To examine changes in the amount of flourishers, languishers, and moderately mentally healthy (MHC-SF), descriptive statistics will be used. Changes in categories will be tested with X^2^-statistics.

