Mediator and moderator analyses will be performed as described by Hayes [94,95]. Mediator analyses will be conducted to investigate which of the specific components of the intervention—positive emotion, use of strengths, optimism, self-compassion, resilience, and positive relations—contribute to its efficacy and mediate overall well-being. Moderator analyses will be conducted to examine which specific subgroups will improve most (or least) on well-being and flourishing from participation in one of the experimental groups. The independent variables of gender, educational level, life-events, personality traits, level of adherence to the intervention, and participation satisfaction will be entered as moderators in regression analyses.

A cost-effectiveness analysis will be conducted from a societal perspective. For each condition, the mean annual health care costs (MCQ), costs due to productivity losses (PCQ), and intervention costs will be calculated on an annual per capita basis for the reference year 2014. All costs will be expressed in Euro (€). The incremental cost-effectiveness ratio (ICER) will be calculated using a bootstrap approach. Then, a cost-effectiveness acceptability curve will demonstrate the probability of the cost-effectiveness of TL-E and TL-I compared to WL, for a range of willingness-to-pay (WTP) ceilings. All tests will be two-sided and will use alphas of 0.05. All data-analyses will be performed with SPSS version 21.0 or higher.

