There could be several limitations that need to be considered in advance. First, our results might not be generalizable to the general Dutch population, since we will use a self-selected sample and apply exclusion criteria on the level of well-being and clinical symptomatology. It is not unlikely that our open recruitment with advertisement in national newspapers will attract mostly highly-educated women. However, we will use a randomization procedure stratified by gender and education, which will create equal distribution of these characteristics to each group and therefore not harm the internal validity of our study. Second, non-adherence to the intervention and drop out from assessments (incomplete data) could occur. Both types of attrition are closely related and may bias our results [98]. Reasons for non-adherence and dropout could be related to individual characteristics (ie, low-educated individuals might find the intervention and/or assessments too difficult), characteristics of the intervention (ie, individuals in the experimental conditions receive the self-help book after baseline and are unaware of the content of the book and type of exercises when they apply for the study), and characteristics of the study (ie, participants will be given instructions and a time schedule) [98]. To gain insight on adherence in our study, participants will be asked about time spent on each module, and the personal counselors will gather reasons for non-adherence mentioned in the email correspondence. Although we expect to find higher adherence rates for individuals in the TL-E condition than has previously been found for Web-based multicomponent PPIs [24,25,27], it could be lower than in face-to-face multicomponent PPIs [20,22,23]. However, our study can only draw conclusions about the comparison of the self-help book with email support to the self-help book without email support. Differences in adherence and efficacy between face-to-face support, email support, and no support warrant attention in future research. Furthermore, to prevent low power due to drop out, we have taken into account an attrition rate of 25% in our power analysis. We will also conduct dropout analysis to identify any selectiveness or characteristics of attrition that may be relevant for real-life implementation of the intervention. Third, the use of senior positive psychology students for the email support can be a risk for the professionalism of our intervention because these students are unexperienced psychologists. We will try to reduce this risk by providing extensive supervision from experienced psychologists and by only selecting students who are thoroughly trained in email support and who have practiced the self-help book. On the other hand, the guidance is primarily process-oriented and advanced clinical counseling skills are therefore not considered necessary. The benefit of using students as counselors is that the intervention costs will be very low. If proven effective, it could be even more effective when implemented in a mental health service with experienced and professional counselors, although this could be disadvantageous for its cost-effectivity. Nevertheless, this needs to be tested in future research.

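### The acceptability curves compare each book arm only with the waiting list, so they can favour book plus email support even when the support adds cost and no benefit

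*Protocol article*

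**What the plan says.** All references are to the Protocol article.

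- **Aim (This Study).** The economic question is whether the book with email support "is a cost-effective approach for enhancing well-being and flourishing compared to a waiting list control group".
- **Analysis (Statistical Analyses).** Annual health care, productivity and intervention costs are computed for each condition. Then "The incremental cost-effectiveness ratio (ICER) will be calculated using a bootstrap approach", with no comparator named. The next sentence does name one: "a cost-effectiveness acceptability curve will demonstrate the probability of the cost-effectiveness of TL-E and TL-I compared to WL", and the curves are drawn "for a range of willingness-to-pay (WTP) ceilings". No WTP threshold, adoption criterion or effect time point is given for the economic analysis.
- **Expectation (This Study).** "We expect that TL-E will be equivalent or superior to TL-I and superior to WL at post-test and 6 months follow-up". Equality of the two book arms is therefore within the hypothesis.
- **Efficacy (Statistical Analyses).** "To examine significant differences between the 3 groups, we will perform repeated measures ANOVA", with Tukey tests after a significant interaction, so TL-E versus TL-I is covered for well-being.
- **Control group.** WL receives the book, and the same information emails as TL-I, after the 6-month assessment. That falls inside the costed year.

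**The concern.** A service choosing among these options can adopt only one. TL-E and TL-I share the book and differ in the emails. TL-E adds weekly counselor replies, a workshop and supervision (Email Support), so it should cost more to deliver. Whether that extra is worth paying for depends on the extra effect and extra cost of TL-E over TL-I. A curve for TL-E against WL mixes the value of the book with the value of the support. If the support does nothing, TL-I delivers the same benefit for less and TL-E is dominated, yet TL-E's curve against WL can still be high.

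Two separate curves against a shared comparator do not give the probability that either book arm is the best of the three. The article says that its results should interest public mental health services and governments. Such a reader could take a high TL-E curve as support for paying counselors when the book alone produced it.

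**Working it through.** **1. The plan's own figure.** For d = 0.40, two-sided 5% and 80% power, n = 2(1.960 + 0.842)²/0.40² = 98.1, so 99 per group. With 25% dropout, 99/0.75 = 132 per group and 396 in total. The Sample Size section reproduces. The article gives no cost-effectiveness figure to reproduce.

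**2. Set-up.** Well-being is in SD units and cost is taken as uncorrelated with effect (an assumption). For a pair of arms with n each, let δ = WTP·d − ΔC and SE² = (2/n)(WTP² + SD_C²), where ΔC is the extra cost and SD_C the cost SD. Two quantities need to be kept apart:
- (A) the height of the bootstrap curve averaged over trials: Φ(δ/(SE√2));
- (B) the height in a trial whose estimates equal the assumed truth: Φ(δ/SE). This is also the probability that a trial's curve lies at or above 0.5.

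**3. Limit of high WTP.** Costs drop out, so no cost assumption is needed, and δ/SE tends to d/√(2/n).

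| Contrast | n per arm | d | d/√(2/n) | (A) | (B) |
|---|---|---|---|---|---|
| TL-E vs WL | 132 | 0.40 | 3.25 | 0.989 | 0.999 |
| TL-E vs WL | 99 | 0.40 | 2.81 | 0.977 | 0.998 |
| TL-E vs TL-I, support adds nothing | 132 | 0 | 0 | 0.50 | 0.50 |

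If the support lowered the effect by 0.10 SD, so that d = 0.30 against WL, (A) at 132 per arm would still be 0.958.

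**4. Finite WTP.** The article gives no euro amounts. Assumed: book EUR 25, email support EUR 200, SD_C EUR 2,000, n = 132, d = 0.40 for both book arms against WL. Quantity (B):

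| WTP per SD (EUR) | TL-E vs WL | TL-E vs TL-I |
|---|---|---|
| 0 | 0.18 | 0.21 |
| 500 | 0.46 | 0.22 |
| 1,000 | 0.74 | 0.23 |
| 2,000 | 0.95 | 0.28 |
| 5,000 | 1.00 | 0.38 |

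Worked row, WTP 2,000: SE = √((2/132)(2,000² + 2,000²)) = 348. Against WL, δ = 800 − 225 = 575 and Φ(1.65) = 0.95. Against TL-I, δ = −200 and Φ(−0.57) = 0.28. Averaged over trials (A), these become Φ(1.17) = 0.88 and Φ(−0.41) = 0.34.

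A three-option simulation at WTP 2,000 gives probabilities of being best of 0.28 for TL-E, 0.71 for TL-I and under 0.01 for WL. Over assumed email costs of EUR 50 to 400 at the same WTP, TL-E versus WL runs from 0.98 to 0.86, and TL-E versus TL-I from 0.44 to 0.13.

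**5. Conditions.** TL-E passes 0.50 against WL only when WTP exceeds (book + email cost)/0.40. For email costs of EUR 50, 100, 200 and 400 that is EUR 188, 313, 563 and 1,063 per SD. If the effect is instead taken at 12 months and WL has caught up (d about 0, book cost cancelling), δ is negative at every WTP and TL-E stays below 0.50 against WL as well, in the sense of both (A) and (B).

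**6. What the added contrast can show.** With 99 per group, d/√(2/99) for d = 0.20 is 1.41, so power for TL-E versus TL-I on well-being is about Φ(1.41 − 1.96) = 0.29.

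**The case against.** The strongest reply is that the analysis answers the question asked. The aim names the waiting list as comparator, the sample size rests on comparisons with it, and the curves follow. That stands: the curves against WL are not an error and should not be dropped.

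Several stronger readings are tempting, and the article does not support them.

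- **That the plan contains a rule declaring TL-E cost-effective.** It fixes no threshold or criterion; it draws curves over a range of ceilings.
- **That TL-E will look cost-effective.** This depends on the three conditions in the working. The 0.99 is a limit in which cost no longer counts, and at low WTP the same assumptions give 0.18.
- **That TL-E versus TL-I is excluded altogether.** The ICER's comparator is left open, costs are computed per condition, and efficacy is compared across all three groups. Point differences between the book arms can be had by subtraction, so dominance on point estimates could be seen. What is not planned is the joint uncertainty of that difference.
- **That the Discussion promises this economic contrast.** The sentence "our study can only draw conclusions about the comparison of the self-help book with email support" versus without it belongs to a passage on adherence and efficacy, and contrasts the trial with face-to-face support. It does not conflict with the economic plan.
- **That the TL-E versus TL-I curve would reliably expose useless support.** The 0.50 ceiling is an average over trials. In the EUR 200 example at WTP 2,000, 28% of trials would still put that curve at or above 0.5, and in the high-WTP limit half would.

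It can also be said that plotting both curves reveals their order. That helps little: in the same example at WTP 5,000 they stand at 0.996 (TL-E) and 0.999 (TL-I), while TL-E versus TL-I is 0.38. Finally, the Discussion expects very low intervention costs with student counselors, so the amount at stake may be small here. It also considers professional counselors, where the cost of support would matter more.

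**Conclusion.** The concern holds in a limited form. The acceptability curves are planned only against WL, which is consistent with the aim. Because the protocol allows TL-E to be merely equivalent to TL-I, those curves can give TL-E a high probability of cost-effectiveness when its distinguishing element returns nothing, and they do not quantify whether the support is worth its cost.

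The cost-free part of the size is the contrast between about 0.99 (0.98 with 99 per arm) against WL and an average of at most 0.50 against TL-I. It rests on the protocol's d = 0.40, no added effect of support, and an effect time point before WL catches up. Every figure at finite WTP also rests on assumed costs, on zero cost-effect correlation and on TL-E costing more overall than TL-I. This is a gap in a non-primary analysis that is worth closing, and it does not invalidate the planned one.

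**What to change.** In the cost-effectiveness paragraph of Statistical Analyses:

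- Keep the curves for TL-E and TL-I against WL, as the answer to the stated aim.
- Resample all three arms together. From the same replicates, report the incremental cost, incremental effect and ICER of TL-E versus TL-I, with a check for dominance.
- Add a three-option acceptability curve giving, at each WTP, the probability that each of WL, TL-I and TL-E has the highest net benefit.
- State the time point of the effect used, given that WL receives the book after 6 months.
- Base any statement that the email support itself is cost-effective on TL-E versus TL-I.

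The cost is a few lines of text and a small extension of the bootstrap. The per-condition costs already planned suffice, and no further participants or data are needed. The downside is a probability for TL-E that is likely to be lower and will be imprecise, because the trial is not powered for TL-E versus TL-I. That imprecision should be reported as such.

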## Results

The data collection will be completed in June 2015.

##  Discussion

This study will investigate the short- and long-term efficacy of a multicomponent PPI (ie, self-help book with tailored email support) on well-being and flourishing. Mediator and moderator analyses will be conducted to explore which theoretically relevant hedonic well-being and eudaimonic well-being components included in the self-help book appear to contribute to its efficacy, and who will benefit most from the intervention. The study will be conducted in The Netherlands in a sample with low or moderate levels of well-being without moderate or severe clinical symptomatology. The results from this study will contribute to the knowledge of evidence-based PPIs, in particular multicomponent PPIs, and will be valuable for public mental health services and governments who are increasingly interested in enhancing well-being in the general population [96,97].

There could be several limitations that need to be considered in advance. First, our results might not be generalizable to the general Dutch population, since we will use a self-selected sample and apply exclusion criteria on the level of well-being and clinical symptomatology. It is not unlikely that our open recruitment with advertisement in national newspapers will attract mostly highly-educated women. However, we will use a randomization procedure stratified by gender and education, which will create equal distribution of these characteristics to each group and therefore not harm the internal validity of our study. Second, non-adherence to the intervention and drop out from assessments (incomplete data) could occur. Both types of attrition are closely related and may bias our results [98]. Reasons for non-adherence and dropout could be related to individual characteristics (ie, low-educated individuals might find the intervention and/or assessments too difficult), characteristics of the intervention (ie, individuals in the experimental conditions receive the self-help book after baseline and are unaware of the content of the book and type of exercises when they apply for the study), and characteristics of the study (ie, participants will be given instructions and a time schedule) [98]. To gain insight on adherence in our study, participants will be asked about time spent on each module, and the personal counselors will gather reasons for non-adherence mentioned in the email correspondence. Although we expect to find higher adherence rates for individuals in the TL-E condition than has previously been found for Web-based multicomponent PPIs [24,25,27], it could be lower than in face-to-face multicomponent PPIs [20,22,23]. However, our study can only draw conclusions about the comparison of the self-help book with email support to the self-help book without email support. Differences in adherence and efficacy between face-to-face support, email support, and no support warrant attention in future research. Furthermore, to prevent low power due to drop out, we have taken into account an attrition rate of 25% in our power analysis. We will also conduct dropout analysis to identify any selectiveness or characteristics of attrition that may be relevant for real-life implementation of the intervention. Third, the use of senior positive psychology students for the email support can be a risk for the professionalism of our intervention because these students are unexperienced psychologists. We will try to reduce this risk by providing extensive supervision from experienced psychologists and by only selecting students who are thoroughly trained in email support and who have practiced the self-help book. On the other hand, the guidance is primarily process-oriented and advanced clinical counseling skills are therefore not considered necessary. The benefit of using students as counselors is that the intervention costs will be very low. If proven effective, it could be even more effective when implemented in a mental health service with experienced and professional counselors, although this could be disadvantageous for its cost-effectivity. Nevertheless, this needs to be tested in future research.

Our study will be the first to investigate the efficacy and working mechanisms of a theory- and research- based multicomponent PPI in the form of a self-help book with email support to enhance well-being and flourishing in the general population. Our study will add to the existing knowledge in that we (1) focus on well-being and flourishing instead of mental illness, (2) use a multicomponent intervention instead of a single-component intervention, (3), integrate some advantages of face-to-face multicomponent PPIs with web-based multicomponent PPIs by using a self-help book with asynchronous and tailored email support, (4) examine the intervention in a population with low or moderate levels of well-being without moderate or severe clinical symptomatology instead of a population with at least moderate clinical symptomatology without any criteria on the well-being dimension of the two-continua model of mental health, and (5) measure and analyze each specific well-being component that is included in the self-help book: positive emotion, use of strengths, optimism, self-compassion, resilience, and positive relations. Taken together, our results will contribute to a new field of multicomponent PPIs for enhancing well-being and flourishing in the general population and highlight a new target population for mental health promotion. If proven effective, our results can be specifically of interest for public mental health and primary care because these health care fields are expanding, while specialist mental health care is diminishing, at least in The Netherlands.

